### Statistical considerations

The primary objectives of this study are to assess the prognostic value and correlation of weekly tumor kinetics (TK) on imaging, and blood biomarkers of head and neck cancers during RT with treatment response and clinical outcomes. Tumor kinetics is the weekly decrease or increase in tumor volume and MR signal after initiation of radiotherapy, again evaluated using MRI. The blood biomarkers of interest are CTCs.

This study will enroll 100 patients. Given the expected toxicity of treatment and patients’ commitment to weekly imaging, it is estimated that 50–60% of enrolled patients may not complete the study. The study will close when we have 40 patients who completed the study. It is anticipated that enrolment will require 24 months to complete. Assuming only 40% of the subjects will complete the study and that 80% of subjects will have complete response, we will have 80% power using a 2-sample t-test with *α* = 0.1 to detect a 1 standard deviation difference between response cohorts with regard to weekly tumor kinetics and blood biomarkers.

We will use graphs and descriptive statistics to evaluate the relationship between TK and CTCs with response. It is expected that 80% of patients will have complete response (CR) to treatment, so the initial analysis will compare those with CR to all others. If we have a sufficient number of patients to separate stable disease (SD) and progressive disease (PD) from partial response (PR), we will conduct analyses separating patients with PR from those with SD/PD. Ninety percent confidence intervals (CIs) will be calculated for mean differences of TK and CTC counts between response cohorts at the time point. Logistic model will be fitted to examine the predictivity of TK and CTCs on response, while adjusting for potential confounders if the data permit. Prior to analysis, data will be transformed as needed.

We will also use generalized linear mixed models (GLMMs) to evaluate TK and CTCs over time and to assess whether a difference exists between patients with CR and those without CR. The primary analysis will use LMMs to assess whether differences exist by response cohort, although if the data permit, GLMMs will also be used to describe the ability of TK and CTCs to predict response. Additionally, if the data do not show a linear trend of TK or CTCs over time, curvilinear models or models using splines will be examined to obtain the best fit for the data.

Secondary objectives include assessing the relationship of TK and CTCs with locoregional control and correlating CTCs with TK during treatment. Locoregional control is defined as 2-year disease-free survival (DFS), and DFS is measured from date of first treatment to date of death, disease progression or recurrence, whichever occurs first. If a patient does not experience progression, recurrence or death, that patient will be censored in the analysis and disease-free survival is measured from date of first treatment until last date of known patient status. Joint longitudinal and survival models will be created to examine the trajectory and intercept of TK and CTCs during radiation therapy with DFS. Longitudinal modeling using a log link function will be used to assess the relationship between TK and the number of CTCs. In this model, weekly number of CTCs will be the outcome and both TK and time will be a predictor variable. The data will be analyzed using Tobit models if we find CTC count is zero-inflated.

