### Evaluation during study

Table 2 summarizes the pre-treatment (initial screening, baseline measures prior to enrollment), on treatment, post-treatment phases of the trial, and the evaluations that would be required during these phases.

**Table 2 Tab2:** Summary of pre-, during and post evaluations during the study

	Baseline	Weekly treatment visits	Follow Up (2–3 months)
Physical examination with or without nasoendoscopy	X	X	X
Weight and BMI	X	X	X
Complete blood count with differential			
- Hemoglobin			
- Neutrophil count			
- Platelet count			
- Monocyte count	X	X	X
Basic Metabolic Panel			
- Electrolytes			
- Liver function tests			
- Albumin			
- ESR			
- CRP	X	X	X
Blood biomarker collection:			
- 10 ml CellSave tube			
- 2 × 10 ml EDTA tubes	X	X	X
Pregnancy test (female of childbearing age)	X		
Contrast CT head and neck	X		X
18F-FDG PET/CT *(optional)*	X		X
MRI of the head and neck	X	X	X

Treatment-related symptom scores and quality of life will be assessed weekly during treatment and at each routine follow up after completion of therapy. Clinical examination and radiological findings indicative of local, locoregional, and/or distant metastatic disease will be recorded.

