Cancer metastasis involves tumor cells being shed from the primary tumor, entering the circulation, and establishing new sites of growth. CTCs can be detected in head and neck cancer [14–16] and can have prognostic significance. CTCs may be present at diagnosis [17, 18] or may have been mobilized into the circulation during treatment [19, 27]. Wu et al. [26] have shown that the recurrence/ metastatic rate in CTC-positive patients was significantly higher than CTC-negative patients with head and neck cancers. In addition, the presence of CTC suggested a worse disease-free survival for HNSCC patients [16, 17, 26]. However, majority of these studies and reviews in head and neck cancer were in the setting of either pre- or post-definitive treatment and there has been no consistency with regards to the optimal timing of CTC testing for prognostic stratification. Simulated case scenarios have also shown no consensus with regards to timing and frequency of CTC testing and the infrequent monitoring of CTCs in the current literature may miss clinically relevant fluctuations in CTC counts [28]. To date, no prospective studies have been performed to identify the optimal frequency for CTC testing and to correlate CTC results with serial radiological response and clinical outcomes in patients with head and neck cancer during definitive radiotherapy. A systemic biomarker (‘liquid biopsy’) that could identify patients who would respond (or not) to local therapy (e.g., serum CTCs as a surrogate of locoregional control) would be actionable for assessing response during and after treatment, and permit response-adapted therapy.

The significance and innovation of the proposed research is that it is the first to correlate on- treatment serial imaging with serial CTC measurements in patients with potentially curable non-metastatic HNSCC. If completed successfully, this study will provide landmark information as to the utility of CTCs (‘liquid biopsy) and tumor-specific functional quantitative imaging changes during treatment to guide personalization of treatment for future patients. Combining the biological information from CTCs and the structural information from MRI may provide more information than either modality alone.

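### Locoregional control is defined as 2-year DFS, so the locoregional secondary objective, as defined, answers a disease-free survival question

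*Protocol article*

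**What the plan says.** The first item under Secondary objectives is to assess MR imaging kinetics as a marker of locoregional control. Statistical considerations restates this for both marker types: "Secondary objectives include assessing the relationship of TK and CTCs with locoregional control".

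The endpoint is then fixed: "Locoregional control is defined as 2-year disease-free survival (DFS), and DFS is measured from date of first treatment to date of death". The full event list is "date of death, disease progression or recurrence, whichever occurs first". Neither the cause of death nor the site of progression or recurrence is restricted.

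The censoring rule is "If a patient does not experience progression, recurrence or death, that patient will be censored in the analysis", at the last date of known status. Residual disease is not named as an event.

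The only outcome model described for this objective uses the same endpoint: "Joint longitudinal and survival models will be created to examine the trajectory and intercept of TK and CTCs during radiation therapy with DFS".

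Elsewhere the article separates failure by site. Evaluation during study says: "Clinical examination and radiological findings indicative of local, locoregional, and/or distant metastatic disease will be recorded". The Background section on nutritional and hematologic markers reports the group's own retrospective work with locoregional control and distant metastasis as distinct outcomes.

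**The concern.** Locoregional control and DFS are different endpoints. DFS is a composite of death and failure at any site; locoregional control concerns failure at the primary site or in the regional nodes. Calling one by the other's name misclassifies patients in two directions: some DFS events are not locoregional failures, and some patients without locoregional control have no DFS event.

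The distinction matters for the intended use. The Discussion puts forward "serum CTCs as a surrogate of locoregional control" and links the markers to escalating or de-escalating local therapy. The same article describes CTCs as part of the route to metastasis, so an association with distant failure is what one would expect biologically. Under the stated definition, that association would be reported as one with locoregional control.

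**Working it through.** **1. The plan's own figure.** The one stated design figure is 80% power for the primary comparison of response cohorts. Inputs from Statistical considerations: 40 completers, 80% CR (32 against 8), a 1 SD difference, alpha 0.1. The noncentrality is 1/√(1/8 + 1/32) = 2.53 with 38 degrees of freedom. Two-sided power is 0.799 by the noncentral t and 0.812 by the normal approximation. The figure reproduces. It does not use the locoregional definition, so nothing below touches it.

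**2. The rules applied to types of patient.**

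| Patient | Under the stated rule | Locoregional control lost? |
|---|---|---|
| Local or regional recurrence or progression | Event | Yes |
| Distant-only failure | Event | No |
| Death without local or regional disease | Event | No |
| PR or SD with residual local disease, never progresses, recurs or dies | Censored, event-free | Arguably yes; the article does not say |

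The second and third rows follow directly from the event list and need no assumption. The fourth follows from the literal censoring rule.

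**3. Ceiling for the fourth row.** The article states: "It is expected that 80% of patients will have complete response (CR) to treatment". The non-CR share is then 20%, and 0.20 × 40 = 8 completers. This is an upper bound: non-CR includes progressive disease, which is a DFS event, and PR or SD patients who later progress or die also become events. No split of PR, SD and PD is given.

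**4. Effect on hazard ratios (assumed inputs).** Let f be the locoregional share of DFS events in the reference (marker-negative) group. The article gives no value, so f is taken as 0.4, 0.6 and 0.8.

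- True locoregional HR 3, no effect on other events: apparent HR = 1 + f × (3 − 1) = 1.8, 2.2, 2.6.
- No locoregional effect, HR 3 for distant failure or death: apparent HR = 1 + (1 − f) × (3 − 1) = 2.2, 1.8, 1.4.

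The definition of f matters. If 40, 60 or 80% is instead the share among all DFS events, with equal marker groups and rare events, the results are about 1.5, 1.9, 2.3 and 1.9, 1.5, 1.2. For example, in the first case at 40%, with reference rates a (locoregional) and b (other), 4a/(4a + 2b) = 0.4 gives b = 3a, and the apparent HR is (3a + 3a)/(a + 3a) = 1.5. The direction is the same under either reading.

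**5. Misclassification (assumed 2-year first-event risks).** Here residual non-progressing disease is counted as a locoregional failure.

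| Locoregional / distant only / death without failure / residual | DFS events not locoregional | Locoregional failures missed | DFS | Locoregional control |
|---|---|---|---|---|
| 10 / 5 / 3 / 2% | 8/18 = 44% | 2/12 = 17% | 82% | 88% |
| 15 / 10 / 5 / 5% | 15/30 = 50% | 5/20 = 25% | 70% | 80% |
| 20 / 15 / 8 / 10% | 23/43 = 53% | 10/30 = 33% | 57% | 70% |

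**The case against.** The best defence is that this is one of six secondary objectives in an observational study that changes no treatment, that the primary power is untouched, and that DFS is a legitimate outcome for the separate objective relating CTCs to later treatment outcomes. All of that stands and limits the reach of the point. It does not remove the contradiction: the article states an explicit definition, so an analysis plan that follows the text inherits it.

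Four stronger readings are tempting, and the documents do not support them.

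- **The objective cannot be answered at all.** Site of failure is recorded, so the question is recoverable; only the endpoint as defined fails to answer it.
- **Residual local disease is declared to be control.** The text only censors such patients without an event and never labels them controlled.
- **Eight of 40 is the expected number so misclassified.** It is a ceiling, for the reasons given in the working.
- **Follow-up is too short for a 2-year endpoint**, because Table 2 ends at 2–3 months and the study closes at 40 completers. That needs a data lock at closure, which is not stated. The article mentions later routine follow-up visits, measures DFS to last known status, and provides for extraction from medical records with data kept for up to 5 years after the study ends. A time-to-event model also uses patients censored before 24 months.

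There is also a fair caution about the remedy. With the assumed 10–20% locoregional progression or recurrence, 40 completers give only 4 to 8 such events (0.10 × 40 to 0.20 × 40), and a cause-specific joint model may be barely estimable. Counting residual disease at the first post-treatment assessment as failure would also overlap heavily with the primary CR comparison. Both bear on how to fix the definition, not on whether to.

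**Conclusion.** The definition is wrong as written. Deaths without local disease and distant-only failures count as loss of locoregional control; this rests on the article's text alone. That residual disease can remain event-free follows from the censoring rule, for at most 8 of 40 completers if the expected 80% CR rate holds. The result would be a DFS association carrying a locoregional label: a true locoregional effect is diluted, and a purely distant one can pass for local.

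The size cannot be fixed from the documents, which give no failure-site rates. A true HR of 3 appearing as 1.8 to 2.6 is an illustration that depends on the assumed reference-group share of 40 to 80%. The other secondary objectives and the primary analysis are not called into question by this point.

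**What to change.** Define locoregional control as the time from first treatment to first local or regional progression or recurrence, using the failure site already recorded. State how residual local or regional disease is counted, and at which assessment, bearing in mind the overlap with the primary response comparison. Treat distant-only failure and death without locoregional failure as competing events and report cumulative incidence; use cause-specific modelling only if event numbers allow. Keep DFS as a separately named endpoint with its joint model.

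At minimum, rename the endpoint DFS throughout and drop the claim about locoregional control.

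The cost is endpoint wording, coding of findings already collected, and fewer events with wider intervals for the locoregional endpoint. The change should be made before outcomes are analysed, since a later redefinition would look data-driven.

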### Hypotheses

Changes in CTC counts and CTC clusters during radiotherapy will have prognostic significance.Changes in tumor signals detected on serial MRI scans during radiotherapy will be predictive of outcomes in head and neck cancer.A relationship can be detected between serial CTC assays and changes in tumor characteristics detected on sequential MRI during radiotherapy.

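### A single TK coefficient in the CTC model mixes differences between patients with week-to-week tracking within a patient; TK should be entered as two terms

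*Protocol article*

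**What the plan says.** All of this is in the Protocol article. The third entry under Hypotheses reads: "A relationship can be detected between serial CTC assays and changes in tumor characteristics detected on sequential MRI during radiotherapy". Under Statistical considerations, one secondary aim is "correlating CTCs with TK during treatment". The method is fixed in two sentences: "Longitudinal modeling using a log link function will be used to assess the relationship between TK and the number of CTCs", and "In this model, weekly number of CTCs will be the outcome and both TK and time will be a predictor variable". A Tobit model replaces this if the counts are zero-inflated.

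TK is defined in the same section: "Tumor kinetics is the weekly decrease or increase in tumor volume and MR signal after initiation of radiotherapy". It therefore varies from week to week within a patient and can also differ persistently from one patient to the next. The article does not say whether the log-link model is marginal or has random effects, and names no other covariate for it. On size, the section states "This study will enroll 100 patients" and "The study will close when we have 40 patients who completed the study".

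**The concern.** Weekly CTCs and weekly MRI are collected together so that the two markers can be related over the course of treatment. The background section on CTCs gives this as a reason for the prospective design, and the Discussion values frequent sampling because sparse sampling can miss fluctuations. A reader will take a significant TK coefficient to mean that CTC counts follow the tumor's response week by week.

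The coefficient need not mean that. Patients whose tumors shrink faster on average may carry systematically more or fewer CTCs for reasons fixed at baseline. Eligibility spans all mucosal head and neck squamous cancers plus unknown primaries, so such differences are plausible. The time term removes the trend shared by all patients, not the persistent differences between them. Two errors could follow: a between-patient difference reported as on-treatment tracking, or a real within-patient link diluted by a between-patient association of opposite sign.

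**Working it through.** **The plan's own figure.** The only design calculation concerns another analysis, the comparison of response cohorts. With 40 completers and 80% complete response, the groups are 40 × 0.8 = 32 and 8. A two-sided two-sample t-test at α = 0.1 for a 1 SD difference has power 0.799 (noncentral t). The stated 80% reproduces and is not affected. No figure is given for the CTC–TK model.

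**The mixture.** Write TK for patient i in week j as m_i + d_ij (patient level plus weekly deviation), and suppose

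log E(CTC_ij) = a + β_B·m_i + β_W·d_ij + γ·time + patient effect.

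A model with one TK term estimates roughly w·β_B + (1 − w)·β_W. The weight w depends on the ICC of TK and on the type of model.

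**Closed form for one case.** Set β_W = 0, total TK variance 1, SD σ of the patient effect on log CTC, and patient-level correlation r between TK and log CTC. With normal patient effects, the slope on the patient level is β_B = rσ/√ICC. Under an independence working correlation w = ICC, so the single coefficient is rσ√ICC.

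- r = 0.5, σ = 1, ICC = 0.6: 0.5 × √0.6 = 0.387 (simulated 0.358)
- r = 0.5, σ = 1, ICC = 0.3: 0.5 × √0.3 = 0.274 (simulated 0.259)
- r = 0.5, σ = 1, ICC = 0.1: 0.5 × √0.1 = 0.158 (simulated 0.134)
- r = 0: 0 (simulated −0.002 and −0.009)

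Exchangeable and random-intercept models give the between-patient part less weight. At r = 0.5 and ICC = 0.6, β_B = 0.5/√0.6 = 0.645. The simulated single coefficients are 0.102 and 0.112, so w is about 0.102/0.645 = 0.16 and 0.112/0.645 = 0.17, against 0.6 under independence.

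**Rejection rates.** From the article: 40 completers, outcome, link and predictors. Assumed: 7 weekly visits, mean CTC count about 1, Poisson counts, σ = 1 unless noted, a mild time trend and β_W = 0. Tests are two-sided at 10%, with 400 replicates (Monte Carlo SE at 10%: √(0.1 × 0.9/400) = 1.5 points). Entries are the percentage of trials in which the single TK term is significant.

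| r | ICC | GEE independence | GEE exchangeable | Random-intercept GLMM |
|---|---|---|---|---|
| 0 | 0.3 | 13 | 12 | 9 |
| 0 | 0.6 | 15 | 13 | 15 |
| 0.3 | 0.3 | 43 | 18 | 17 |
| 0.3 | 0.6 | 56 | 21 | 23 |
| 0.5 | 0.1 | 44 | 17 | 13 |
| 0.5 | 0.3 | 75 | 21 | 18 |
| 0.5 | 0.6 | 83 | 37 | 35 |
| 0.5 (σ = 0.5) | 0.6 | 72 | 54 | 48 |
| 0.7 | 0.6 | 99 | 53 | 58 |

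With TK split into patient mean and weekly deviation, the deviation coefficient averages about 0 throughout and is significant in 8–17%. The excess over 10% for GEE is small-sample error in the sandwich variance; it appears without confounding too (12–14%).

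**Masking.** With β_B = 0.5, β_W = −0.3, a within-patient SD of TK half the between-patient SD (ICC = 1/(1 + 0.5²) = 0.80) and an exchangeable GEE, one set of assumed values gives a single coefficient of −0.10 with 44% power. The split model gives −0.30 with 96%. In another simulated setting with the same within-patient slope, the single coefficient falls to about 0, with 22% power against 83%.

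**Cost of splitting.** If the two slopes are equal, pooling is efficient. In one such scenario power falls from about 73% for the single term to about 50% for the deviation term.

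**The case against.** The strongest reply is that the hypothesis is not worded as within-patient only. A finding that patients with more CTCs have slower shrinkage would also be a relationship between the two markers. Several stated uses, such as selecting and stratifying patients, are between-patient. This stands. A significant single coefficient driven by patient averages reflects a real association, and it misleads only if read as week-by-week tracking.

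A reader might infer that the model would show a link even where CTCs have nothing to do with tumor change. The documents do not support that. The bias needs average TK and CTC level to be correlated across patients; with r = 0 none was found. A reader might also infer that large false-positive rates are to be expected. Rates of 60–80% or more under an exchangeable GEE arise only at ICCs of about 0.8–0.9. These are hard to justify for TK, a weekly change measure that already removes much of the difference in starting tumor size. High rates at lower ICCs need an independence working correlation, which the article does not name; the models it names elsewhere in the section are mixed models.

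The article is also a condensation, and parameterization is often settled in an analysis plan. That lowers the weight of the point but does not remove it. The sentence does specify the model and names TK itself as the predictor, so someone following it would enter one term. Entering two TK terms would be compatible with it, which makes the change easy.

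**Conclusion.** The point holds in limited form. As written, the CTC–TK model does not separate between-patient from within-patient association, and its coefficient cannot by itself support a statement that CTCs track MRI change during radiotherapy.

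The size is uncertain. At an assumed r of 0.5, it runs from near the no-confounding baseline (ICC 0.1–0.3, mixed or exchangeable model) to 35% or more at ICC 0.6, with far higher rates under independence. The number of visits, ICC, correlation, CTC mean and patient SD are all assumptions, and the simulations use complete data. This is a secondary analysis in an observational study that leaves treatment unchanged. The change is worth making because the answer is otherwise ambiguous, not because the result is bound to be wrong.

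**What to change.** In the CTC–TK model, replace TK by two covariates: the patient's mean TK and the weekly deviation from that mean. Keep time, and use the same two terms if the Tobit model is needed. Report both coefficients. Base any statement that CTCs track on-treatment MRI change on the deviation term, and any statement about differences between patients on the mean term. State whether the model is marginal or mixed.

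The article expects that "it is estimated that 50–60% of enrolled patients may not complete the study", so patients' means will often cover different weeks. Compute the mean over the on-treatment weeks actually observed and adjust for time flexibly, so that the two terms do not merely reflect which weeks were seen.

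The cost is a sentence or two of analysis text and one more covariate, with no extra data. The drawback is lower power for the deviation term than for a pooled term if the two slopes are in fact equal.
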